### Study objectives

This proposal describes a study that is currently being implemented in eight public and private ambulatory clinic pharmacies in Qatar. Our hypothesis is that a patient-specific structured smoking cessation program delivered by smoking cessation-trained ambulatory pharmacists would be significantly more effective in helping smokers stop smoking and achieving long-term smoking abstinence than brief unstructured pharmacist-delivered advice.

We also hypothesize that quitting smoking would lead to significant improvement in health-related quality of life.

The study objectives are:Primary: To test the effect of a face-to-face structured patient-specific smoking cessation program delivered by trained ambulatory pharmacists on smoking cessation rates in QatarSecondary: To assess the change in health-related quality of life in quitters vs. non-quittersSecondary: To explore the resource utilization of implementing the smoking cessation program as delivered by the ambulatory pharmacists in Qatar. This is a cost analysis of the overall cost of running the proposed patient-specific cessation program, including cost-effectiveness analyses.

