### Data analysis

The CONSORT guidelines will be followed when analyzing the study data. Demographics and other variables related to smoking and quality of life will be summarized using frequency distributions (for categorical variables) and means with standard deviations (for numeric variables) and will be compared between the two study arms using the chi-squared test (or alternatively the Fisher’s exact test for small cell counts) for categorical variables and the independent *t*-test (or alternatively the Wilcoxon rank sum test for non-normally distributed variables) for numerical variables.

The main outcome will be continuous abstinence at 12 months as self-reported and verified by the CO test. The percentages of participants achieving the main outcome will be computed and compared between the two groups using the chi-squared test. Moreover, the difference in the proportions of continuous abstinence at 12 months between the two study arms (with 95% confidence intervals) will be computed along with the number needed to treat. Multiple logistic regression will be used to obtain the odds ratio of the main outcome between the two study arms adjusting for any imbalances in demographics or other baseline smoking-related variables. Moreover, mixed effects logistic regression, with pharmacy-level random effect, will be considered to adjust for the possible pharmacy effect if it existed. The intent-to-treat principal will be used in the analysis whereby participants who will be lost to follow-up will be classified as smokers and included in the main analysis. This includes those who were removed from the study because they could not tolerate NRT side effects. A sensitivity analysis following that of Borelli, Hogan et al. will be done where the outcome has three possible categories: abstinence, no abstinence and dropout [48]. The suggested multinomial model will allow assessing factors affecting abstinence as well as factors affecting dropout. This will aid in understanding who might need more support during the intervention. Similar analyses for the primary outcome will be done at 3 and 6 months (but do not include verification of abstinence using CO tests).

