To assess the participants’ health-related quality of life, SCQOL (smoking cessation quality of life) ratings for each question will be translated into scores. A total health-related quality of life score and a domain-specific score will be calculated at baseline, 3 months, 6 months and 12 months for each participant in the intervention and control groups. The change in the total and domain-specific quality-of-life score from baseline will be calculated for each participant at 3, 6 and 12 months and analyzed using linear mixed models, which will include the quitting (quitters and non-quitters) factor and time factor (at 3, 6 and 12 months) and their interaction.

There is no interim analysis planned for this trial. Statistical analyses will be conducted using the Statistical Package of Social Sciences (IBM-SPSS®), version 21. In all analyses, the level of significance will be set at 5%.

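### The longitudinal quality-of-life model contrasts quitters with non-quitters and names neither arm nor any confounder, so it can show an association but not the hypothesised effect of quitting

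*Protocol article*

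**What the plan says.** The Study objectives section of the protocol article states: "We also hypothesize that quitting smoking would lead to significant improvement in health-related quality of life". The matching secondary objective, and the quality-of-life item under Outcome measures, compare change from baseline in quitters with change in non-quitters at 3, 6 and 12 months.

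Under Data analysis, a total score and domain scores "will be calculated at baseline, 3 months, 6 months and 12 months for each participant in the intervention and control groups". The changes from baseline are then analysed by "linear mixed models, which will include the quitting (quitters and non-quitters) factor and time factor", with the interaction of the two. No arm term and no covariate is named for this model. For the primary outcome the same section does name a covariate-adjusted model, "adjusting for any imbalances in demographics or other baseline smoking-related variables".

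One more sentence bears on the point. The opening of Data analysis says that "Demographics and other variables related to smoking and quality of life will be summarized using frequency distributions" or means with standard deviations, and that these variables "will be compared between the two study arms using the chi-squared test" or the t-test and their alternatives. No time point is given.

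**The concern.** Randomisation protects a comparison of arms. It does not protect a comparison of people who quit with people who did not. Smokers who are healthier or less dependent may be more likely to quit and also more likely to report improving quality of life.

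The document itself points to a second route, through the programme:

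- **Training.** Under Study pharmacists' training, pharmacists are given coping strategies to pass on, including lifestyle changes meant to lower stress and raise quality of life.
- **Intervention arm.** First session and Follow-up sessions provide tailored lifestyle strategies and, for those who have quit, help with stress, cravings and social pressures.
- **Control arm.** Control group provides 5-10 minutes of unstructured advice plus written material, with no follow-up sessions.

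The programme may therefore raise both quitting and quality of life. In a model without arm, that benefit is partly credited to quitting. A significant quitting term would be read as confirming the causal hypothesis when selection or the programme could have produced it.

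**Working it through.** **Inputs.** Sample size calculation gives 12-month abstinence of 3% (control) and 15% (intervention), two-sided alpha 5%, power 90% and 118 per group. The document gives no SD or target difference for SCQOL, so effects below are in SD units of the change score and are assumptions.

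**1. The plan's own figure.** With mean rate 0.09 and no continuity correction:

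n = [1.960 x sqrt(2 x 0.09 x 0.91) + 1.282 x sqrt(0.03 x 0.97 + 0.15 x 0.85)]² / 0.12² = (0.793 + 0.507)² / 0.0144 = about 117.4, so 118 per group. The figure reproduces, with power 90.1%.

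**2. Composition of the two groups at planning rates.**

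| | Intervention | Control | Total | Share from intervention |
|---|---|---|---|---|
| Quitters | 118 x 0.15 = 17.7 | 118 x 0.03 = 3.54 | 21.24 | 83.3% |
| Non-quitters | 118 x 0.85 = 100.3 | 118 x 0.97 = 114.46 | 214.76 | 46.7% |

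**3. Carry-over of a direct programme effect.** Suppose the programme raises quality of life by d SD in everyone who receives it, and quitting does nothing. The expected difference between quitters and non-quitters is (0.833 - 0.467) x d = 0.37d. For d = 0.5 this is 0.18 SD. The imbalance comes from the gap in quit rates, so it is largest when the programme works as hoped.

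**4. How often a spurious difference would be declared significant.** The standard error of the contrast is sqrt(1/21.24 + 1/214.76) = 0.227 SD. If quitting has no effect, a confounded difference of a given size (assumed range, from any source) is significant at 5% with probability:

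| Confounded difference | Rejection probability |
|---|---|
| 0.2 SD | 14% |
| 0.3 SD | 26% |
| 0.5 SD | 59% |

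**5. What a comparison by arm could show.** If quality of life changes only through quitting, with effect d, the expected arm difference is (0.15 - 0.03) x d = 0.12d. Its standard error is sqrt(2/118) = 0.130 SD.

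| Assumed quitting effect | Arm difference | Power at 118 per arm | n per arm for 80% power |
|---|---|---|---|
| 0.5 SD | 0.060 SD | 7% | 4,361 |
| 0.8 SD | 0.096 SD | 11% | 1,704 |

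The quitter contrast has about 59% power for a true 0.5 SD effect. The two contrasts estimate different quantities, so this is no ranking of their merit.

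**The case against.** The strongest reply is that the quitter contrast is the deliberate objective, that it is far better powered for a quitting effect than a comparison by arm, and that a condensed article need not list every covariate of a secondary model. Much of this stands, and it rules out several stronger readings that a reader might infer.

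- **That no comparison of quality of life between arms is planned at all.** The opening sentence of Data analysis includes quality-of-life variables among those compared between arms. It is grouped with demographics and probably means baseline, but it is not limited to baseline. What can be said is that the longitudinal model and the quality-of-life outcome specify no arm effect on change.
- **That the model makes no adjustment.** The response is change from baseline, so each participant's own starting value is subtracted. The listed terms need not be a closed list, and an analysis plan that is not shown may add covariates.
- **That the randomised comparison is thrown away.** A comparison by arm asks whether the programme improves quality of life, which is a different question, and it may have very low power. It would not rescue the quitting hypothesis. Nor is it certain to be free of bias: intervention participants who do not tolerate NRT leave the study at follow-up sessions that controls do not attend, so missing scores could differ by arm.
- **That omitting baseline SCQOL biases the contrast.** This holds if both groups regress to a common mean. If self-selected groups have stable, different levels, the change score can be the sounder form and adding baseline can introduce bias. The document does not settle which applies.
- **That the many domain scores tested at 5% give a calculable rate of false positives.** The scores and visits are correlated, and handling of multiplicity for secondary scores is commonly left to the analysis plan.

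What the reply does not remove is the mismatch between a causal hypothesis and a model whose stated terms cannot separate quitting from programme or selection.

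**Conclusion.** The concern holds in limited form. Followed as written, the longitudinal analysis can show that quitting and quality of life are associated. It cannot show that quitting leads to improvement. Arm is a confounder that the document itself makes plausible, and a direct programme effect of d SD would carry over as about 0.37d SD.

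That figure rests on the planning rates, which are 7-day point prevalence at 12 months. The model does not say which abstinence definition makes a quitter, and other definitions or visits would change the split. It also assumes that the direct effect is equal in quitters and non-quitters. If it went only to intervention participants who quit, the carry-over would be 0.83d, and an arm term alone would not remove it. The size of d and of any selection effect is unknown.

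This is a secondary outcome and the primary comparison is untouched. The change is worth making because it is cheap and affects how the result will be read.

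**What to change.** 1. **Quitter v non-quitter model.** Add randomised arm and baseline factors already collected at the initial appointment: FTND, cigarettes per day, age, and health status from the medical history. Report it with and without baseline SCQOL, since neither form is unbiased in general for self-selected groups.
2. **Wording.** State the hypothesis and its conclusion as an association between quitting and change in quality of life. Covariates reduce confounding but do not make the contrast causal.
3. **Model by arm.** Add a linear mixed model with arm, time, arm x time and baseline SCQOL as the randomised estimate of the programme's effect on quality of life. Scores are already computed "for each participant in the intervention and control groups". State that it answers a different question and has low power if quality of life changes only through quitting.

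The cost is revised analysis wording, one more model and a weaker causal statement. No new data are needed.

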The workshop covered the following: smoking epidemiology and risks, benefits of quitting, a transtheoretical model for behavior change as applied to smoking cessation, the necessary elements for documentation in the patient smoking cessation profile, behavioral modification techniques, classification of smokers according to their stage of change (5 stages: precontemplation, contemplation, preparation, action and maintenance), nicotine replacement therapy (NRT: nicotine patch, lozenge and gum), patient counseling techniques, development of a personalized action plan, use of the exhaled carbon monoxide test, detailed instructions on the program methodology and other needed elements.

In addition, the pharmacists’ training workshop included training the pharmacists on how to follow the study protocol exactly. The study team walked the pharmacists through the study protocol including how to randomly allocate participants to the intervention and control groups, how to deliver the intervention and how to deal with control patients.

During the training workshops, emphasis was also placed on the importance of behavioral and lifestyle modifications. Pharmacists were instructed to encourage smokers who are anticipating quitting to identify the situations that may increase their risk of smoking such as having smokers within the household or at the workplace as well as getting into stressful situations. After identifying these situations, the pharmacists were provided with information they could give to smokers about strategies to improve coping including lifestyle changes to decrease stress and improve QoL, removing visual cues for smoking and staying away from these situations that normally make patients want to smoke [37]. In addition, the pharmacists were trained to provide the smokers with information about what to expect during quit attempts and to address any individual concerns that the smokers may have [38]. Furthermore, they were advised to encourage the smokers to notify family and friends of the plan to quit and to ask for their support [37].

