Participant counseling and interviewing techniques were also part of the training workshops. To enhance learning, the pharmacists applied these techniques using patient role-plays in small groups. Topics that were reviewed included counseling skills, verbal and nonverbal communication skills including use of empathy and active listening, use of open-ended and priming questions, verification of patient understanding, overcoming of communication barriers, communication with difficult patients, communication with patients not interested in discussing smoking cessation and use of strategies to improve medication adherence.

Documentation was an important element of the workshop. The pharmacists were trained to document the patient’s smoking, medical and medication history, basic demographic characteristics, staging, assessment, education, counseling, follow-up and the personalized action plan to quit smoking. In addition, they were instructed on how to fill in the Fagerstrom test for nicotine dependence (FTND). The FTND is a six-item questionnaire designed to assist the healthcare professional in determining a patient’s degree of nicotine dependence [39]. This questionnaire has already been used in smoking-related research studies in the Middle East area [40,41]. Furthermore, they were instructed to measure the smoker’s health-related QoL using the Smoking Cessation Quality of Life (SCQOL) questionnaire. This instrument was developed and validated for use in smoking cessation [42,43] and has already been used in previous studies that tested the effectiveness of a pharmacist-delivered smoking cessation program [16]. This questionnaire tackles a total of 13 general and smoking cessation-specific quality-of-life domains including physical functioning, role-physical, bodily pain, general health, vitality, social functioning, role-emotional, mental health, social interactions, self-control, sleep, cognitive functioning and anxiety [43].

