**Participant flow during the study.**

#### Control group

Participants in the control group receive 5-10 min of unstructured brief smoking cessation counseling by the pharmacist (emulating current practice). In addition, they are provided with educational materials about smoking cessation and are offered nicotine replacement therapy (NRT). Before dispensing the NRT, the study pharmacist ensures that the participant does not have any contraindications to nicotine therapy and is not taking any medication that would interact with NRT. The choice of the NRT dosage form (patch or lozenge) depends on the participant’s previous experience, preference and adverse effect profile. The NRT dosage schedule and duration of therapy are similar to those in the intervention group. Control participants are not asked to attend any follow-up sessions.

The education materials address the following topics: the adverse effects of smoking, benefits of smoking cessation, the methods of quitting, setting the quit date, coping with nicotine withdrawal symptoms, getting emotional and social support, and monitoring the blood pressure and pulse when using NRT and avoiding relapse.

The study team invests a good deal of time orienting the study pharmacists on their role and training them on how to deal with the control and intervention groups. Part of that orientation is on how ‘not’ to provide any intervention to the control subset of smokers.

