The economic evaluation will be undertaken via decision analytic modeling, where a decision tree will be structured to follow the different options and consequences in the management pathways. For each of the participants, the proposed model may include five possible treatment outcomes depending on whether participants quit smoking, and if they do, after what duration. Smokers will be initially assigned to one of two pathways depending on whether they quit smoking at enrollment. Smokers who do not quit at enrollment will be further followed until assigned to one of two pathways, depending on whether the smoker quits smoking after 3 months or not. If not, smokers will be followed up until further assigned to one of two pathways, based on whether they quit smoking after 6 months or not. Those who do not quit by then will be followed up until assigned to one of two pathways depending on whether they quit at 12 months of follow-up or not, which will be the end of follow-up in any case. Smokers who quit at enrollment or after 3, 6 or 12 months will each be followed up separately until the end of the study. Based on this, in addition to data on resources consumed and their monetary values, the model will generate a weighted average cost for patient cessation and quality-of-life adjustment. As per the general decision analysis principles, this will be calculated as the sum-product of the costs of the management outcomes and the respective probabilities.

The costs of managing the single episode of smoking cessation will be compared among different management options and against budgeted costs of clinics/government institutions.

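### The SCQOL mixed model compares quitters with non-quitters without a term for randomised arm, so part of any direct programme effect on quality of life would be credited to quitting

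*Protocol article*

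**What the plan says.** Under Study objectives the protocol article states a causal secondary hypothesis: "We also hypothesize that quitting smoking would lead to significant improvement in health-related quality of life". Study objectives and Outcome measures both define the quality-of-life comparison as quitters against non-quitters, not arm against arm.

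The Data analysis section calculates SCQOL scores for participants in both arms and analyses change from baseline with linear mixed models, "which will include the quitting (quitters and non-quitters) factor and time factor (at 3, 6 and 12 months) and their interaction". Neither arm nor any other covariate is named for these models. For abstinence, the same section does name adjustment for baseline imbalances and a possible pharmacy random effect.

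Under Study pharmacists' training, pharmacists are given material to pass on about "strategies to improve coping including lifestyle changes to decrease stress and improve QoL". The SCQOL domains listed there include "mental health, social interactions, self-control, sleep, cognitive functioning and anxiety". Under Control group, controls receive 5-10 minutes of brief advice, educational materials and an NRT offer, and "Control participants are not asked to attend any follow-up sessions".

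**The concern.** Quit status arises after randomisation and is what the programme is meant to change. If the counselling also moves SCQOL by a route other than quitting, for example through coping with stress, then arm is a common cause of quitting and of the outcome. A model without arm assigns part of that direct effect to the quitting coefficient.

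The hypothesis concerns what quitting does. With the model as written, a programme that eased stress without changing anyone's smoking status could still raise the chance of a positive result for quitting. The quality-of-life model also contains no contrast that randomisation protects. Arm is known for every participant, so this one source of bias can be removed at almost no cost.

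**Working it through.** **Inputs from the protocol article (Sample size calculation).** 12-month abstinence of 3% (control) and 15% (intervention), two-sided alpha 5%, power 90%, 118 per group, 1:1 allocation.

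**Assumptions.**
- The direct effect g of the programme on SCQOL change, in SD units, is not in the documents. The range taken is 0.1 to 0.5.
- The 3% and 15% are 7-day point prevalence rates and stand in for quit status in the SCQOL model.
- All 236 participants contribute a score, and one time point is considered.

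**1. Reproduce the planned sample size.** Pooled variance, no continuity correction:

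n = [1.96·√(2·0.09·0.91) + 1.282·√(0.03·0.97 + 0.15·0.85)]² / 0.12² = 117.4, rounded up to 118. The stated figure is reproduced.

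**2. Arm mix by quit status.**

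| | Intervention | Control | Intervention share |
|---|---|---|---|
| Quitters | 118 × 0.15 = 17.7 | 118 × 0.03 = 3.5 | 0.833 |
| Non-quitters | 118 × 0.85 = 100.3 | 118 × 0.97 = 114.5 | 0.467 |

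**3. Share of a direct effect passed to quitting.** 0.833 − 0.467 = 0.366. Equivalently, 0.25 × 0.12 / (0.09 × 0.91) = 0.366.

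**4. Bias and false-positive rate when quitting has no true effect.** The bias is 0.366 × g. The SE of the quitter contrast is √(1/21.2 + 1/214.8) = 0.227 SD. The false-positive rate is P(|Z + bias/SE| > 1.96). The simulation used 4,000 trials of 118 per arm, analysed by least squares.

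| Assumed g (SD) | Bias (SD) | False-positive rate, formula | Simulated, no arm term | Simulated, arm term added |
|---|---|---|---|---|
| 0.2 | 0.07 | 6% | 5.5% | 4.6% |
| 0.3 | 0.11 | 8% | 7.6% | 4.2% |
| 0.5 | 0.18 | 13% | 11.9% | 5.6% |

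At g = 0.1 the bias is 0.04 SD. With arm in the model the simulated bias was close to zero throughout.

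**5. Sensitivity to the quit rates.** The share is 0.28 at 5% v 15%, 0.17 at 8% v 15%, and 0 if the rates are equal. At assumed rates of 20% v 40% it is 0.25 × 0.20 / (0.30 × 0.70) = 0.24.

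**6. Cost of adding arm.** The correlation of arm with quit status is 0.12 / (2·√(0.09·0.91)) = 0.21. The variance inflation is 1 / (1 − 0.21²) = 1.046, so the standard error widens by √1.046 = 1.02, about 2%.

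**The case against.** The quitter contrast is the declared objective, and a comparison by arm answers a different question. The article says what the models will include, which does not exclude further covariates, and an unseen analysis plan might add them. The programme is built for cessation, and quality of life enters as one aim of its lifestyle strategies. Control materials also cover withdrawal, emotional and social support, and NRT is offered in both arms. Total session time is only about 70 to 80 minutes (30 + 20 + two sessions of 10 to 15), while SCQOL is measured up to 12 months, so a lasting direct effect of 0.5 SD is not evident. At 0.2 SD the bias is about a third of its standard error (0.07/0.227).

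Much of this stands, and it limits the point's importance. It does not remove the point: the article names the terms of this model, arm is not among them, and the hypothesis is causal. The between-arm comparison of quality-of-life variables earlier in Data analysis has no stated time point, reads most naturally as baseline, and in any case does not adjust the quitter contrast.

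Three stronger readings are tempting and not supported:

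- A reader might infer that the programme's whole direct benefit is credited to quitting. On the planning rates it is about 37% of an effect whose size is unknown.
- A reader might infer that the biased estimate enters the economic evaluation, because there "the model will generate a weighted average cost for patient cessation and quality-of-life adjustment". That section does not say that the mixed-model estimate is an input.
- A reader might infer that adding arm makes the quitter contrast causal. It does not. Baseline health and dependence may still confound it. The Follow-up sessions section ties stress relief to participants who have quit, and a benefit confined to intervention quitters would stay in the quitting coefficient. With about 3.5 expected control quitters, an arm-by-quitting term could hardly be estimated.

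**Conclusion.** The point holds as a minor improvement to a secondary analysis. The named terms omit a variable that is expected to be strongly associated with quit status by design and has a plausible separate route to the outcome. The 37% share rests on the protocol's 3% and 15%. The bias of 0.07 to 0.18 SD and the false-positive rates of about 6% to 13% rest also on direct effects of 0.2 to 0.5 SD, which are assumptions. If the direct effect is negligible, so is the bias. The primary abstinence analysis is unaffected.

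**What to change.** In the Data analysis paragraph on quality of life:

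- Add randomised arm and arm-by-time to the SCQOL mixed models, for the total and the domain scores.
- Report the randomised contrast of SCQOL change by arm at 3, 6 and 12 months beside the quitter contrast.
- Describe the quitter contrast as an association, and say that adjusting for arm does not remove other confounding or the effect of support given only to intervention quitters.

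This takes a sentence or two and no new data. The standard error of the quitting effect widens by about 2%.
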